### 2.6. Data Collection—Preliminary Results

Various databases are available in the CRESPI study and are illustrated in Figure S2 (online supplement). Data checking and preliminary analyses are in progress.

#### 2.6.1. Characteristics of Cleaning Tasks in the Daycares

The characteristics of cleaning tasks are reported in Table 2.

#### 2.6.2. Characteristics of Daycare Workers

A preliminary descriptive analysis was conducted on the 309 daycare workers whose questionnaires were recorded as of 1 November 2022 (Table 3). The average age of the workers, almost exclusively women, was 43 years, and most of them were never smokers and taking care of the children. Around 15% and one third of the workers have ever had asthma and eczema, respectively.

#### 2.6.3. Characteristics of Children

A preliminary description on the 501 children whose questionnaires were recorded as of 1 November 2022 was performed (Table 4). The average age of the children was 23 months. Approximately 30% of them had wheezing, which is consistent with the prevalence for this age group [29,69].

### 2.7. Biological Assessment

#### 2.7.1. Nasal Swabs for Characterization of Nasal Microbiota

Parents of all children aged ≤ 12 months enrolled in the CRESPI cohort were asked to collect two nasal swabs in their child. The first swab was collected shortly after the child’s daycare visit. The second swab is collected at age 24 months. Swab collection is performed using a standardized protocol tested and validated in the US MARC-35 study [70]. At both collections, we mail the parents a kit to do the swab at home, including collection material (Pediatric FLOQ-Swab [Copan, Brescia, Italy] and a vial containing viral transport media), a specimen transport bag, and a pre-paid mailing box addressed to CSTB. The collection consists of rubbing the swab gently against the inner wall of each nostril and to insert the swab in a provided vial. Detailed instructions are provided to the parents, and a video is available on the study website (https://crespi.vjf.inserm.fr/index.php/ressources/#tutoriels; accessed on 16 May 2023). We ask the parents to place the vial in a specimen transport bag, and to keep it in the refrigerator until they can ship it to CSTB (at their earliest convenience). Samples are stored at CSTB at −80 °C until the end of each collection. After each collection, all samples are shipped on dry ice to Baylor College of Medicine (Houston, TX, USA) for microbiota profiling.

#### 2.7.2. Buccal Cells for Characterization of the DNA Methylation

Parents of children enrolled in the CRESPI cohort were asked to collect buccal swabs in their child using a simple, quick, and non-invasive protocol (via a cytobrush) with a kit specially designed to collect DNA from children by their parents (ORAcollect for Pediatrics/ OC-175, DNAGenotek). A simple step-by-step pictorial description of the procedure was given to parents to correctly perform the collection, which consists of rubbing the inside of each child’s cheek back and forth about 10 times. The sample was sent by the parents to CSTB and stored at room temperature for less than 1 year. DNA was then extracted by a company recognized for this expertise (i.e., DNA Genotek, Qiagen). DNA methylation is measured by a state-of-the-art Illumina chip (EPIC chip) allowing to cover 850,000 CpG sites by the CNRGH (French National Center of Human Genomics research), a laboratory internationally recognized in the genomics and postgenomics field. This is the most widely used method in epidemiological studies.

### 2.8. Statistical Analyses

Statistical analyses will be performed to evaluate the associations between environmental exposures in daycares, evaluated through complementary and precise methods (e.g., measurements of VOCs and SCOVs, DCP emissions, smartphone application), and respiratory health of workers and children, after adjustment for potential confounders. The main outcomes will be current asthma in workers, and wheezing outcomes in children. Among children, longitudinal wheezing phenotypes will be defined by longitudinal latent class analysis (statistical clustering approach), making full use of data collected by questionnaire during follow-up (first monthly and then every six months), from infancy to age 4-years. The impact of DCP exposures on asthma and other respiratory symptoms such as nocturnal cough will be specifically evaluated among adults and children.

For example, among workers, associations of the frequency of use in daycares of cleaning products (such as sprays and wipes) with current asthma and nocturnal cough will be evaluated by logistic regressions, adjusted for age, smoking status, body mass index and educational level. Among children, associations of cleaning products used in daycares with wheezing and nocturnal cough will be evaluated by logistic regressions, adjusted for gender, age, parental smoking status and educational level. Dependency between children from the same daycare will be taken into account by generalized estimating equation models.

Power calculations for exposure variables and respiratory outcomes in children are presented in Table 5. The minimum detectable Odds Ratio for 80% power is close to values observed in previous studies for cleaning exposure at home and respiratory outcomes in children [12].

Analyses will also be conducted to study the relationships between daycare environment, nasal microbiota, and the respiratory health of children. First, we will characterize environmental (dust) and nasal microbiota profiles using clustering approaches, such as partitioning around medoids, using weighted UniFrac distance [59,71]. Then, we will use multinomial logistic regressions: (1) to determine the association of environmental exposures in daycare (number and characteristics of occupants, environmental microbiota (settled dust), indoor air quality, cleaning/disinfection practices) with baseline and longitudinal nasal microbiota profiles; and (2) to determine the association of baseline and longitudinal nasal microbiota profiles with respiratory health (wheezing trajectories from infancy to age 4 years). Finally, we will examine the modulating and/or mediating role of nasal microbiota in the association between environmental exposures in daycare and respiratory health, using stratified analyses and formal test for statistical interaction in multivariable models, and mediation analyses based on the counterfactual framework [72,73].

Analyses will also be conducted to evaluate associations between exposures in daycares and DNA methylation among children. Regarding the epigenetic study, among the multiple exposures to cleaning products measured in CRESPI, we will target in this analysis the exposures associated with respiratory health in first association studies in CRESPI data. An agnostic approach (Epigenome Wide Association Studies, EWAS) based on robust linear regressions adjusted for potential confounders with methylation levels as the response variable and exposure concentration as the predictor will be used. The EWAS results will then be examined by enrichment analysis to determine whether the identified CpG sites are over-represented in specific genomic regions or in specific biological pathways. In addition, association studies simultaneously taking into account several adjacent CpG sites (regions) will be applied to search for differentially methylated regions (DMRs) in relation to exposures to cleaning products.

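### Daycare clustering is provided for the children's models only; the worker model for a main outcome has no stated allowance for it, so its intervals will be somewhat too narrow if outcomes correlate within daycares

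*Protocol article*

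**What the plan says.** All of this stands in section 2.8 of the protocol article.

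- Main outcomes: "The main outcomes will be current asthma in workers, and wheezing outcomes in children".
- Worker model, offered as an illustration in which the exposure is how often products are used: "with current asthma and nocturnal cough will be evaluated by logistic regressions, adjusted for age, smoking status, body mass index and educational level". Those four covariates are the whole stated model; daycare does not appear.
- Children: logistic regression for wheezing and nocturnal cough, followed by the article's only sentence on clustering: "Dependency between children from the same daycare will be taken into account by generalized estimating equation models".
- Microbiota, in the next paragraph: "Then, we will use multinomial logistic regressions". Part (1) relates daycare exposures (dust microbiota, indoor air quality, cleaning practice) to nasal profiles. Part (2) is planned "to determine the association of baseline and longitudinal nasal microbiota profiles with respiratory health".
- Epigenome-wide study (EWAS): "robust linear regressions adjusted for potential confounders with methylation levels as the response variable and exposure concentration as the predictor will be used", followed by a region-level analysis.

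Neither the microbiota nor the EWAS paragraph has its own statement on daycare clustering.

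**The concern.** Workers and children were sampled through the same daycares. The authors recognised the dependency this creates and wrote a remedy, but its wording reaches only one of the two populations. The omission falls on a main outcome.

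Workers of one daycare use the same stock (Table 2: one to nine products per daycare). Section 2.3.1 says that air and dust were measured in a single room per daycare, so each measured concentration has one value for all its workers. Section 2.8 lists those measurements among the exposures to be related to workers' health. When both exposure and outcome are correlated within daycares, a logistic regression that ignores the grouping understates the standard error, and the error runs towards false positives.

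The EWAS has the same structure when its predictor is a measured air or dust concentration. The term robust linear regression usually refers to outliers or unequal variance, and need not mean robust to correlation within daycares. At an epigenome-wide threshold, a small understatement of variance has a much larger relative effect than at 5%.

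**Working it through.** The article gives no ICC, design effect or error rate for these models, and Table 5 covers power in children only. There is therefore no plan figure to reproduce. Every ICC below is an assumption.

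**Inputs from the article.** 108 daycares visited (2.2); 309 workers recorded (2.6.2), about 320 expected (section 3); 501 children recorded (2.6.3); 850,000 CpG sites (2.7.2).

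**Formulas.** With mean cluster size m and an exposure constant within daycare, the design effect is DE = 1 + (m − 1) × ICC. The real type I error of a nominal 5% test that ignores clustering is 2 × (1 − Φ(1.96/√DE)).

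**Workers, fully shared exposure.** m = 309/108 = 2.86.

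| Assumed ICC | DE | True SE / naive SE | Type I error, equal clusters | Type I error, cluster-size CV 0.6 (assumed) |
|---|---|---|---|---|
| 0.01 | 1.02 | 1.01 | 5.2% | 5.3% |
| 0.05 | 1.09 | 1.05 | 6.1% | 6.7% |
| 0.10 | 1.19 | 1.09 | 7.2% | 8.4% |

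The last column uses DE = 1 + ((1 + CV²) × m − 1) × ICC. With 320 workers (m = 2.96) and equal clusters, the type I errors are 5.2%, 6.1% and 7.3%.

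**Workers, exposure only partly shared.** Frequency of use varies between workers of a daycare. Replace ICC by the product of outcome ICC and exposure ICC: DE = 1 + 1.86 × ICC(outcome) × ICC(exposure). For outcome ICC 0.05 to 0.10:

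- exposure ICC 0.3 (assumed): DE 1.03 to 1.06, type I error 5.3% to 5.7%;
- exposure ICC 0.5 (assumed): DE 1.05 to 1.09, type I error 5.5% to 6.1%.

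**EWAS with a daycare-measured concentration.** The article states no threshold; assume 0.05/850,000, for which z = 5.42. The false-positive rate per site is multiplied by 2 × (1 − Φ(5.42/√DE)) divided by 0.05/850,000.

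- If all 501 children contribute (m = 4.64): ICC 0.01, 0.05, 0.10 gives DE 1.04, 1.18, 1.36 and multipliers of about 1.7, 10 and 58. If the same ICC held at every site, expected false hits would be 0.09, 0.5 and 2.9 instead of 0.05.
- At an assumed 2.5 children per daycare: about 1.3, 2.9 and 7.3.

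**Microbiota part (1).** Section 2.7.1 limits swabs to children aged 12 months or less. Taking the 180 children in the under-one group of Table 4 as a proxy, m = 180/108 = 1.67. At ICC 0.05 to 0.10, DE is 1.03 to 1.07 and type I error 5.4% to 5.8%, even for a fully shared exposure.

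**The case against.** The strongest reply is that the article is silent and does not assert independence. Its worker and child models are offered as examples, it condenses a fuller protocol and analysis plan, and the children's model is itself called logistic regression before GEE is added in a separate sentence. So naming a regression family need not settle the variance method. This stands against any claim that independence is specified. It does not remove the point about workers: the article does address dependency, and words the remedy for children alone.

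A reader might also infer that the microbiota and EWAS models ignore clustering outright. The text does not support that. Both samples are children, so the GEE sentence can be read to cover them; its place before those paragraphs, and its being a different estimator from robust linear regression, leave this open.

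A third tempting reading is that all these models rest on daycare-level exposures. That is wrong for two of them. Product use was collected from individual workers in face-to-face questionnaires (2.3.3), and Table 3 shows mixed jobs, so frequency of use can differ within a daycare. Microbiota part (2) uses the child's own nasal profile. The label is right for measured concentrations and for the daycare exposures in microbiota part (1).

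Finally, the EWAS multipliers depend on an assumed ICC, threshold and sample size, and the EWAS is a complementary project, not a main outcome.

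**Conclusion.** The point holds for workers. The stated model for a main outcome makes no allowance for daycare, while the children's model beside it does. Too-narrow intervals follow only if worker outcomes correlate positively within daycares and the exposure is at least partly shared; the article does not show that errors are too small as a matter of fact. With about three workers per daycare the effect is modest: real type I error of roughly 5.2% to 7.2% for assumed ICCs of 0.01 to 0.10, a fully shared exposure and equal cluster sizes. It is less for frequency of use and somewhat more with uneven clusters.

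For microbiota model (1) and the EWAS, the finding is an ambiguity to be closed. It matters most in the EWAS because of the extreme threshold. Overall severity is moderate to minor.

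**What to change.** 1. Reword the dependency sentence so that it covers workers as well as children from the same daycare. Fit the worker models as GEE logistic regressions with daycare as the cluster and robust standard errors.
2. State that daycare clustering also applies to the later models with daycare-level exposures: cluster-robust variance for multinomial model (1), and a daycare random intercept or daycare cluster-robust errors (with a small-sample correction) for the EWAS and the region-level analysis.
3. Say what robust means in the EWAS.

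The cost is a sentence or two of text and a model option. No new data are needed. Intervals become slightly wider: for workers with a fully shared exposure, by about 1% to 9% over the assumed ICC range with equal clusters.

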## 3. Discussion

While early exposure to irritant or sensitizer DCP may have an impact on the respiratory health of young children, few studies have evaluated this topic [12,13]. Among adults, exposure to DCP is a well-known occupational asthma risk factor, but its impact on respiratory health has never been studied among daycare workers [12,18]. The CRESPI cohort has been designed to address these research gaps by collecting detailed exposure data with novel tools and using standardized methods to evaluate respiratory health in ~540 children attending daycares and ~320 daycare workers.

Current knowledge is insufficient to provide recommendations regarding the use of safe DCP, despite a strong demand from both consumers and workers. A recent study suggested that the household use of DCP labelled as ‘green’ might induce fewer risks for current asthma, compared to the use of conventional products [74]. Moreover, an association was observed between weekly household use of DCP classified with a poor Ménag’score^®^ (D and E), a health risk assessment score allowing to inform the consumers by a simple labelling on toxicity of cleaning products ingredients (https://www.60millions-mag.com/2019/08/27/produits-menagers-nocifs-les-premiers-pas-du-menag-score-16406; accessed on 16 May 2023), and more frequent asthma symptoms among 100 women [48]. The use of such a score, with a simple and intuitive labelling, might allow to improve public health prevention. However, additional studies are needed to confirm these recent findings. Moreover, studying DCP as mixtures of complex substances rather than each substance individually is helpful for a better understanding of the health impact of DCP [48]. Data from the CRESPI cohort will allow to further study these recent research topics.

Nevertheless, a weakness of the CRESPI study is that the original purpose of including 1000 children and 600 daycare workers was not reached, linked to the COVID-19 pandemic. A total of 922 parents and 776 workers have responded positively to participate in the study, but only 51% of them have sent their questionnaires and consent as of November 2022. The recruitment and visits of daycares were stopped during the first lockdown and then restarted at a very slow pace (Online supplement; Figure S1). The pandemic might in part explain a low participation rate and return of questionnaire/consent forms from both workers and parents. Participants told us that they did not have time to participate in CRESPI due to the COVID-19 health crisis. Moreover, potential selection bias may have occurred in the inclusion phase for both workers and children. To evaluate selection bias among workers, we will compare the use of DCP among participants and non-participants, using data from the smartphone application and the ingredient list DCP database available for all workers present during the one-day daycare visits. To evaluate selection bias among parents, we will compare information from the reply-coupon of participants who sent their consent and questionnaires to those who did not.

The originality of the CRESPI study lies in the fact that it is the first epidemiological survey focusing on the effect of early environmental exposure to DCP in daycares on respiratory health in the first years of life, as well as the first one which will allow to evaluate associations between occupational daycares exposures and health among workers. Moreover, this cohort was set up through multidisciplinary collaborations between epidemiologists, chemistry researchers, and computer scientists at the cutting edge of technology. The visits of the daycares have been successful; the daycare acceptance rate was higher than initially expected, all workers present the one-day daycare visit accepted to scan DCP used, and all the measurements were conducted as planned. CRESPI benefits from complementary and innovative technologies, via smartphone applications, to improve assessment of daycare exposure to DCP. Indoor pollution (aldehydes and VOCs in indoor air, SVOCs in settled dust) was measured in each daycare. This provides a uniquely precise database characterizing the daycare environment, a common early-life environment for many children. Another strength of the CRESPI study is to collect data on the respiratory health of children and workers through standardized methods (questionnaires) and innovative tools. Moreover, longitudinal data with repeated evaluation of respiratory health will be available in a relatively large population of more than 500 children, which will permit a better understanding of impact of DCP on children′s respiratory health.

## 4. Conclusions

The goal of visiting 100 randomly selected daycares was reached; 9985 products (861 unique ones with barcodes scanned) have been recorded in daycares. A large set of data is available related to these products, with their composition, their VOC, and SVOC emissions, and the indoor concentrations of some of these VOCs and SVOCs, which is unique to date. Inclusion was closed in December 2022 and the follow-up of children is funded until June 2023. Furthermore, we aim to pursue the follow-up of children included in the CRESPI cohort beyond 2023 (conditional to funding) to explore the incidence and evolution of respiratory health of the children to at least the age of 6. Such a cohort, with a rich evaluation of exposure to specific DCP substances and of respiratory health, is essential to evaluate the impact of DCP used in daycares on asthma and to thereafter take adequate preventive measures for both workers and children.

## Figures and Tables

**Figure 1 ijerph-20-05903-f001:**
[figure not shown]
Illustration of some environmental measurements performed in daycares. (**a**) Indoor air sampling for aldehyde and VOC analysis; (**b**) Settled dust sampling with cellulose cartridge for SVOC analysis; (**c**) Settled dust sampling with Mitests^®^ for microbiota analysis.

**Figure 2 ijerph-20-05903-f002:**
[figure not shown]
Summary of recruitment—preliminary results. (**a**) Summary of daycare workers recruitment; (**b**) Summary of children recruitment. Around 37% of workers (776/2100) agreed to participate at the first step (**a**). This response rate can be considered as underestimated—as only 1586 workers were at work the day of the visit—and is rather around 49% (776/1586). For the parents, 16% of them (922/5790) have responded positively and 12% (700/5790) have declined to participate. We have not received replies for 72% (4168/5790) of the parents (**b**). However, finally, only ~50% of them returned their questionnaires.

**Table 1 ijerph-20-05903-t001:** Distribution of daycares by administrative department (*n* = 108).

Paris Metropolitan Area	Randomized Daycares (n = 102)			Non-Randomized Daycares (*n* = 6)	
	Expected	Complete Visit	Incomplete Visit *	Pilot Visits	Other Visits
75	34	33	1	2	
92	26	25			
93	17	15	1		1
94	12	13		2	
77	7	7			1
91	4	7			
Total	100	100	2	4	2

* Environmental measurements not performed or cleaning products used by workers not scanned.

**Table 2 ijerph-20-05903-t002:** Characteristics of cleaning tasks in the daycares (*n* = 106 daycares).

Characteristics	*n* (%)
Time for floor wet cleaning (multiple answers)	
in the morning, before children arrive during the day, in presence of children during the day, without children (during the nap) in the evening, after children depart	40 (37.7) 7 (6.6) 11 (10.4) 66 (62.3)
Window opening during floor cleaning	
during cleaning only after cleaning only during and after cleaning never missing information	52 (49.1) 1 (0.9) 31 (29.2) 6 (5.7) 16 (15.1)
Time for furniture cleaning (multiple answers)	
in the morning, before children arrive during the day, in presence of children during the day, without children (during the nap) in the evening, after children depart	29 (27.3) 29 (27.3) 29 (27.3) 72 (67.9)
Window opening during furniture cleaning	
during cleaning only after cleaning only during and after cleaning never missing information	62 (58.5) 3 (2.8) 29 (27.4) 10 (9.4) 2 (1.9)
Number of DCP used in daycares	
1–2 3 4 5 6–9	16 (15.1) 26 (24.5) 30 (28.3) 16 (15.1) 18 (17.0)

**Table 3 ijerph-20-05903-t003:** Characteristics of daycare workers—preliminary results (n = 309 workers).

Characteristics	n (%)
Women	299 (98.4)
Age, years	
Mean ± Standard Deviation [min; max]	43.2 ± 10.2 [18.4; 64.8]
Job	
Children care Cleaner/Cook/Clothes washing Administrative support Others	202 (66.4) 19 (6.3) 46 (15.1) 37 (12.2)
Educational level	
<high school diploma high school to 2-level university >3-level university	98 (32.5) 91 (30.1) 113 (37.4)
Smoking status	
Never smoker Ex-smoker Smoker	194 (64.0) 73 (24.1) 36 (11.9)
Respiratory symptoms	
Asthma symptom score, last 12 months 0 >1 Ever Asthma Asthma attacks, last 12 months Woken by an attack of coughing, last 12 months	261 (85.9) 43 (14.1) 45 (14.8) 21 (7.0) 49 (16.2)
Eczema, ever	105 (34.4)

**Table 4 ijerph-20-05903-t004:** Characteristics of children from daycares—preliminary results (n = 501 children).

Characteristics	*n* (%)
Girls	235 (47.1)
Daycare group	
<1 year old	180 (36.1)
1–2 years old	144 (28.9)
>2 years old	131 (26.3)
Grouped sections	43 (8.7)
Age, months	
Mean ± Standard Deviation	22.7 ± 10.3
Respiratory symptoms	
Wheezing	157 (31.5)
Wheezing and breathlessness	36 (7.2)
Woken by breathlessness	20 (4.2)
Attack of coughing during the night	135 (27.5)
Bronchiolitis	205 (42.6)
Asthma attack	59 (12.1)
Eczema	77 (15.4)

**Table 5 ijerph-20-05903-t005:** Minimum detectable Odds Ratio for 80% power, according to exposure and respiratory outcomes in children (examples for wheezing and nocturnal cough).

	Cleaning, Daycare *	Sprays, Daycare ^†^
Wheezing (31%)	1.51	1.70
Nocturnal cough (27%)	1.56	1.77

Calculation performed with the hypothesis of final population size of 600 children. * For exposure prevalence of cleaning during the day: 46% vs. cleaning tasks performed in the morning before children’s arrival, according to Wei et al. [36]. ^†^ For exposure prevalence of 18%, according to Wei et al. [36].

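### Table 5's detectable odds ratios assume about 60 more children than the closed cohort has and appear to come from a hazard-ratio formula, so power at those values is about 60–68%, not 80%

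*Protocol article*

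**What the plan says.** Table 5 of the protocol article is titled "Minimum detectable Odds Ratio for 80% power, according to exposure and respiratory outcomes in children". It prints 1.51 (daytime cleaning) and 1.70 (sprays) for wheezing at 31%, and 1.56 and 1.77 for nocturnal cough at 27%. Exposure prevalences of 46% and 18% come from a cited earlier survey. The footnote says "Calculation performed with the hypothesis of final population size of 600 children". No significance level, sidedness or formula is given.

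Section 2.8 plans adjusted logistic regressions, with generalized estimating equations for children who share a daycare. It concludes from Table 5: "The minimum detectable Odds Ratio for 80% power is close to values observed in previous studies".

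On the size of the cohort, the Discussion gives "540 children attending daycares and ~320 daycare workers", and the abstract agrees. Section 2.4 expects final numbers very near those already shown in Figure 2. The Conclusions state "Inclusion was closed in December 2022 and the follow-up of children is funded until June 2023". Table 4 describes 501 children recorded by 1 November 2022.

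**The concern.** Two features of Table 5 do not fit the rest of the article. Its sample size is larger than a cohort that can no longer grow, and its odds ratios are smaller than an odds-ratio calculation gives from the table's own inputs. Table 5 is the article's only power statement, and section 2.8 relies on it to say that the study can detect effects of the size seen before. If the figures are optimistic, a reader will credit the children's analyses with more sensitivity than they have, which matters most when an association is not found.

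**Working it through.** **Inputs.** From Table 5: outcome prevalence P = 0.31 or 0.27, exposure prevalence e = 0.46 or 0.18, N = 600, power 80%. From the abstract and Discussion: N about 540. As a cross-check, section 2.4 counts 863 returned questionnaires and consents, and 540 + 320 = 860. Assumed because not stated: two-sided alpha 0.05 (z = 1.960; z for 80% power = 0.842). Children are treated as independent throughout.

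**Step 1: reproduce the printed values.** The events-based formula is

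ratio = exp[(1.960 + 0.842) / √(N·P·e·(1−e))].

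Wheezing and cleaning: 600 × 0.31 × 0.46 × 0.54 = 46.20; √46.20 = 6.797; 2.802/6.797 = 0.412; exp(0.412) = 1.510. The four cells come to 1.510, 1.707, 1.555 and 1.773, against the printed 1.51, 1.70, 1.56 and 1.77. With the Table 4 counts (157/501 and 135/501) in place of the rounded percentages they are 1.507, 1.702, 1.556 and 1.774, which round to all four printed entries.

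**Step 2: what that formula leaves out.** It treats N·P as a number of events for a hazard ratio. Near the null, the information on a log odds ratio is N·P·(1−P)·e·(1−e). For wheezing and cleaning the extra factor is 0.69: 46.20 × 0.69 = 31.88; √31.88 = 5.646; 2.802/5.646 = 0.496; exp(0.496) = 1.64 instead of 1.51. With outcomes of 27–31% the omission is material.

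**Step 3: power at the printed odds ratios.** Two-proportion test, pooled variance under the null and unpooled under the alternative, with p1 = OR·p0/(1 − p0 + OR·p0) and p0 the unexposed risk. The 31% and 27% can be read in two ways: as the risk in the unexposed, or as the overall prevalence, which is how Table 4 reports the matching figures. On the overall reading, p0 is solved from (1−e)·p0 + e·p1 = P.

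Wheezing and cleaning, unexposed reading, N = 600 (276 exposed, 324 not): p0 = 0.310, p1 = 0.404, pooled risk 0.353, both standard errors 0.0392. Power = Φ[(0.0942 − 1.960 × 0.0392)/0.0392] = 67.2% before rounding. On the overall reading p0 = 0.269, p1 = 0.358 and power is 64.4%.

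| Cell | Printed OR | Power, N=600 (overall / unexposed reading) | Power, N=540 (overall / unexposed reading) |
|---|---|---|---|
| Wheezing, cleaning | 1.51 | 64.4 / 67.2% | 59.9 / 62.6% |
| Wheezing, sprays | 1.70 | 67.4 / 68.4% | 63.0 / 64.0% |
| Cough, cleaning | 1.56 | 67.4 / 71.3% | 62.9 / 66.7% |
| Cough, sprays | 1.77 | 71.2 / 72.7% | 66.9 / 68.4% |

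A simulation of the Wald log-odds-ratio test (200,000 runs per cell) gave 64–72% at 600 and 60–68% at 540.

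**Step 4: separate the two causes.** Keeping the Step 1 formula and changing only N to 540, power at the printed values is 75.7, 75.1, 76.3 and 75.5%, and the detectable ratios become 1.54, 1.76, 1.59 and 1.83. The sample size alone therefore costs 4 to 5 percentage points; the rest comes from the formula.

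**Step 5: detectable odds ratios at 80% power (unexposed to overall reading).**

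| Cell | Printed | N=600 | N=540 |
|---|---|---|---|
| Wheezing, cleaning | 1.51 | 1.61–1.64 | 1.65–1.69 |
| Wheezing, sprays | 1.70 | 1.84–1.85 | 1.90–1.91 |
| Cough, cleaning | 1.56 | 1.64–1.68 | 1.68–1.73 |
| Cough, sprays | 1.77 | 1.87–1.89 | 1.93–1.95 |

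**The case against.** The best defence is that Table 5 is neither arbitrary nor concealed. Its values do follow at N = 600 from a recognised formula, the 600 is labelled a hypothesis, the Discussion admits that the recruitment targets were missed, and no design decision still hangs on the table. All of that stands. It limits the point to reporting, but it does not make the printed odds ratios detectable with 80% power in this cohort.

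Several stronger readings are tempting, and the document does not support them.

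- *The table cannot be reproduced, or was built on a one-sided test.* Step 1 reproduces it at two-sided 5%. An odds-ratio calculation at one-sided 5% with 600 children (unexposed reading) gives 1.53, 1.72, 1.55 and 1.75, which is close but misses every cell.
- *The missing 60 children explain the shortfall.* Step 4 shows that they explain the smaller part.
- *One exact figure is the true power.* The result depends on how 31% and 27% are read and on an unstated alpha. If one-sided 5% was meant, the unexposed reading gives about 74–78% at 540.
- *Table 2 refutes the 46% exposure prevalence.* The floor rows ("40 (37.7) 7 (6.6) 11 (10.4) 66 (62.3") suggest at most 18 of 106 daycares (17%) wet-clean floors in the daytime. But Table 5 speaks of cleaning in general, and Table 2 also reports daytime furniture cleaning in 29 daycares with children present and 29 during the nap. Multiple answers were allowed, so that is between 29/106 (27%) and 58/106 (55%), a range that contains 46%. Whether evening cleaning falls in either arm depends on the cited survey's definition, which is not shown.
- *The sentence about previous studies is false.* The cited values are not in the document, so only a recheck can be asked for.

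**Conclusion.** The point holds as a matter of sample size and formula. The assumed 600 exceeds the article's own figure by about 60 children (10% of those assumed), and with inclusion closed the gap will not fill. For the planned odds-ratio analysis, the printed values carry about 64–73% power at 600 children and 60–68% at 540, against the stated 80%. These figures assume two-sided 5%, Table 5's own prevalences and independent children. That the table came from an events-based hazard-ratio formula is an inference from the numerical match. The shortfall for an odds ratio does not depend on that inference.

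No allowance is made for clustering. The article gives no intraclass correlation, so the effect of daycare clustering cannot be sized here; for exposures fixed by the daycare, positive correlation would lower power further.

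**What to change.** State the significance level, sidedness and formula under Table 5. Recompute the four cells for an odds ratio with about 540 children, and say whether 31% and 27% are overall or unexposed risks. With the current prevalences and two-sided 5%, the entries would be about 1.65–1.69 and 1.90–1.91 for wheezing, and 1.68–1.73 and 1.93–1.95 for nocturnal cough. Label them as before any allowance for daycare clustering, or add an allowance with its assumed correlation stated. Then check the section 2.8 comparison with previous studies against the new values and reword it if it no longer holds. The cost is one table, its footnote and one sentence; data collection and the planned models are unaffected, but the stated sensitivity becomes less favourable.
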